### **8.3.2      *Secondary Endpoint Analysis***

Descriptive statistics (mean, standard deviation [SD], score range) of the measures of adolescent acceptability and appropriateness as well as parental acceptability, appropriateness, feasibility, affordability and accessibility at week 12 will be reported.

### **8.3.3      *Exploratory Endpoint Analysis***

Descriptive statistics (mean total scores, score ranges, standard deviations) and figures will be used to portray the results of baseline (T1) and 12 weeks (T4) assessments of household food insecurity, household nutrition insecurity, parental financial coping strategies, parental time demands, and parental financial wellbeing.

Descriptive statistics (mean total score, score range, SD) will be used to portray adolescents' treatment-related symptoms and chemotherapy-induced alterations in taste.

Qualitative descriptive approaches will be used to identify themes in the interviews with adolescents and parents about their experiences with MTM-Kids meals and recommendations for needed improvements.

---

Treatment exposures, scores on assessments of symptom and chemotherapy induced alterations in taste will be used to qualitatively explore linkages between symptoms, alterations in taste, and themes in the interview data.

#### **8.3.4**     *Interim Analysis*

When 5 adolescent-parent dyads (formative test) have completed study requirements, their data will be analyzed as described above, study processes and the MTM-Kids intervention will be refined as needed, and then the validation test will commence.

## **9 STUDY MANAGEMENT**

### **9.1 Required Documentation**

Before the study can be initiated at any site, the following documentation must be provided to the University of North Carolina.

- A copy of the official IRB approval letter for the protocol and informed consent
- IRB membership list or Federalwide Assurance (FWA) number.
- CVs and medical licensure for the Principal Investigator and any sub-investigators who will be involved in the study.
- The Investigator's signature documenting understanding of the protocol and providing commitment that this trial will be conducted according to all stipulations of the protocol.

### **9.2 Institutional Review Board (IRB) Approval and Consent**

It is expected that the IRB will have the proper representation and function in accordance with federally mandated regulations. The IRB will approve the consent form and protocol.

In obtaining and documenting informed consent, the investigator should comply with the applicable regulatory requirement(s) and should adhere to Good Clinical Practice (GCP) and to ethical principles that have their origin in the Declaration of Helsinki.

Before recruitment and enrollment onto this study, the subject will be given a full explanation of the study and will be given the opportunity to review and discuss the consent form and the Investigator or research staff (as appropriate) will answer any questions the subject has related to the study. Each consent form must include all the relevant elements currently required by the FDA Regulations and local or state regulations. Once this essential information has been provided to the subject and the investigator is assured that the subject understands the implications of participating in the study, the subject will be asked to give consent to participate in the study by signing an IRB approved consent form.

Prior to a subject's participation in the trial, the written informed consent form should be signed and personally dated by the subject and by the person who conducted the informed consent discussion.

### **9.3 Registration Procedures**

All subjects must be registered by the UNC study coordinator before enrollment to study. Prior to registration, eligibility criteria must be confirmed with the UNC Study Coordinator.

---

## 9.4 Adherence to Protocol

Except for an emergency situation in which proper care for the protection, safety, and well-being of the study subject requires alternative treatment, the study shall be conducted exactly as described in the approved protocol.

### 9.4.1 *Protocol Deviations/Violations*

A protocol deviation is any unplanned variance from an IRB approved protocol that:

- Is generally noted or recognized after it occurs;
- Has no substantive effect on the risks to research participants;
- Has no substantive effect on the scientific integrity of the research plan or the value of the data collected;
- Did not result from willful or knowing misconduct on the part of the investigator(s).

An unplanned protocol variance is considered a violation if the variance meets any of the following criteria:

- Has harmed or increased the risk of harm to one or more research participants;
- Has damaged the scientific integrity of the data collected for the study;
- Results from willful or knowing misconduct on the part of the investigator(s);
- Demonstrates serious or continuing noncompliance with federal regulations, State laws, or University policies.

If a deviation or violation occurs, please follow the guidelines below:

*Protocol Deviations:* UNC will record the deviation in OnCore®, and report to any sponsor or data and safety monitoring committee in accordance with their policies.

*Protocol Violations:* Violations should be reported as per the IRB's requirements. They must also be recorded as a deviation in OnCore®.

Any events that meet the criteria for "Unanticipated Problems (UPs)" must also be reported to the IRB. Examples of such UPs include a lost or stolen laptop computer that contains sensitive study information. If the UP is the result of a protocol deviation, then the deviation must also be recorded in OnCore®.

---

## **9.5 Study Files and Record Retention**

Study documentation includes all eCRFs, data correction forms or queries, source documents, Sponsor correspondence to Investigators, and regulatory documents (e.g., protocol and amendments, IRB correspondence and approval, signed subject consent forms).

Source documents include all recordings of observations or notations of clinical activities and all reports and records necessary for the evaluation and reconstruction of the clinical research study.

Government agency regulations and directives require that all study documentation pertaining to the conduct of a clinical trial must be retained by the study investigator. Study documents should be kept on file until three years after the completion and final study report of this investigational study.

## **9.6 Obligations of Investigators**

The Principal Investigator is responsible for the conduct of the clinical trial at the site in accordance with Title 21 of the Code of Federal Regulations and/or the Declaration of Helsinki. The Principal Investigator is responsible for personally overseeing the treatment of all study subjects. The Principal Investigator must assure that all study site personnel, including sub-investigators and other study staff members, adhere to the study protocol and all FDA/GCP/NCI regulations and guidelines regarding clinical trials both during and after study completion.

The Principal Investigator at each institution or site will be responsible for assuring that all the required data will be collected and entered into the eCRFs. At the completion of the study, all eCRFs will be reviewed by the Principal Investigator and will require his/her final signature to verify the accuracy of the data.

## **9.7 Data and Safety Monitoring Plan**

The Principal Investigator will provide continuous monitoring of subject safety in this trial with periodic reporting to the Data and Safety Monitoring Committee (DSMC).

Meetings/teleconferences will be held at a frequency dependent on study accrual. These meetings will include the investigators as well as study coordinators, data coordinators, regulatory associates, and any other relevant personnel the principal investigators may deem appropriate. At these meetings, the research team will discuss all issues relevant to study progress, including enrollment, safety, regulatory, data collection, etc.

The team will produce summaries or minutes of these meetings. These summaries will be available for inspection when requested by any of the regulatory bodies charged with the safety of human subjects and the integrity of data including, but not limited to, the oversight of Office of Human Research Ethics (OHRE) Biomedical IRB, the Oncology Protocol

---

Review Committee (PRC) or the North Carolina TraCS Institute Data and Safety Monitoring Board (DSMB).

The UNC LCCC Data and Safety Monitoring Committee (DSMC) will review the study on an annual basis at the time of IRB annual review, with the option to exempt from the study from future review. The UNC PI will be responsible for submitting the following information for review: 1) safety and accrual data; 2) significant developments reported in the literature that may affect the safety of subjects or the ethics of the study; 3) preliminary response data; and 4) summaries of team meetings that have occurred since the last report. Findings of the DSMC review will be disseminated by memo to the UNC PI, PRC, the UNC IRB and DSMB.

## **10 AUDITING AND MONITORING**

The UNC LCCC will serve as the coordinating center for this trial. Data will be collected through a web based clinical research platform, REDCap. All data will be collected and entered into REDCap by research coordinators from UNC LCCC.

The site will provide direct access to source data/documents for trial-related monitoring, audits, IRB/IEC review, and regulatory inspection. As an investigator-initiated study, this trial may be audited. Any corrective and preventive action plans (CAPAs) resulting from the audit will be reviewed by the LCCC compliance committee for acceptability. All data will be monitored, and source data will be verified on selected subjects. Database queries will be issued on an ongoing basis on all subjects. The site should respond to data queries within 14 days of receipt.

## **11 AMENDMENTS**

Should amendments to the protocol be required, the amendments will be originated and documented by UNC LCCC. It should also be noted that when an amendment to the protocol substantially alters the study design or the potential risk to the subject, a revised consent form may be required.

The written amendment, and if required the amended consent form, must be sent to UNC's IRB for approval prior to implementation.

## **12 STUDY DISCONTINUATION**

Both Lineberger Comprehensive Cancer Center and the Principal Investigator reserve the right to terminate the study at the investigator's site at any time. Should this be necessary, Lineberger Comprehensive Cancer Center or a specified designee will inform the appropriate regulatory authorities of the termination of the study and the reasons for its termination, and the Principal Investigator will inform the IRB/IEC of the same. In terminating the study, Lineberger Comprehensive Cancer Center and the Principal Investigator will assure that adequate consideration is given to the protection of the subjects' interests.

## **13 CONFIDENTIALITY**

All information generated in this study is considered highly confidential and must not be disclosed to any person or entity not directly involved with the study unless prior written consent is gained from Lineberger Comprehensive Cancer Center. However, authorized regulatory officials, IRB/IEC personnel, Lineberger Comprehensive Cancer Center and its authorized representatives are allowed full access to the records.

Identification of subjects and eCRFs shall be by initials, screening and treatment numbers only. If required, the subject's full name may be made known to an authorized regulatory agency or other authorized official.

## 15.2 APPENDIX II – Study Measures

### 15.2.1 ADOLESCENT SURVEYS

#### 15.2.1.1 Adolescent Medical Record Abstraction Form T1 (To be completed by study team)

1. Study ID#: \_\_\_\_
  2. Today's date: \_\_/\_\_/\_\_
  3. Diagnosis:
    - a. Acute Lymphoid Leukemia
    - b. Acute Myeloid Leukemia
    - c. Hodgkin lymphoma
    - d. Non-Hodgkin lymphoma
    - e. Brain or other central nervous system cancer
    - f. Neuroblastoma or other peripheral nerve tumor
    - g. Hepatic tumor
    - h. Osteosarcoma
    - i. Ewing sarcoma
    - j. Rhabdomyosarcoma
    - k. Non-Rhabdoid sarcoma
    - l. Germ cell or gonadal tumor
    - m. Wilm's tumor
    - n. Other (please specify): \_\_\_\_\_
  4. Diagnosis date: \_\_/\_\_/\_\_
  5. Treatment protocol number: \_\_\_\_\_
  6. Start date:
  7. Chemotherapies received to date: (list) \_\_\_\_\_
  8. Current cycle: \_\_
  9. Current cycle start date: \_\_/\_\_/\_\_
  10. Radiation therapy: No \_\_ Yes\_\_
  11. If yes, radiotherapy field \_\_\_\_\_
  12. Current height: \_\_\_\_\_. \_ centimeters
  13. Current weight: \_\_\_\_\_. \_ kilograms
-

### 15.2.1.2 Adolescent Acceptability and Appropriateness

These questions ask your opinions about the Medically Tailored Meals for Kids (MTM-Kids) program. Please select the response that best fits your thoughts.

| Acceptable                                                               | Completely disagree | Disagree | Neither agree nor disagree | Agree | Completely agree |
|---------------------------------------------------------------------------------|---------------------|----------|----------------------------|-------|------------------|
| The meal choices appeal to my family.                                           |                     |          |                            |       |                  |
| We liked the variety of meal choices                                            |                     |          |                            |       |                  |
| With MTM-Kids, our family felt my child's healthcare team cared about my family |                     |          |                            |       |                  |
| We recommend MTM-Kids                                                           |                     |          |                            |       |                  |
| Appropriate                                                              | Completely disagree | Disagree | Neither agree nor disagree | Agree | Completely agree |
| MTM-Kids is fitting for families like mine.                                     |                     |          |                            |       |                  |
| 10 meals per week is appropriate                                                |                     |          |                            |       |                  |
| Weekly is the right timing for deliveries                                       |                     |          |                            |       |                  |
| The meal size was suitable                                                      |                     |          |                            |       |                  |

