#### **3.2 Secondary**

- 3.2.1 *Participant-reported acceptability, appropriateness, feasibility, affordability, and accessibility of the MTM-Kids intervention is defined as mean overall scores for the 4 item measures of each domain (appendix X)  $\geq 3$  (agree) for 70% of adolescents (acceptability and appropriateness) and 70% of parents (acceptability, appropriateness, feasibility, affordability, and accessibility) at week 12 (T4).*

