### 4.1 Study Intervention

We will enroll 5 adolescent + 5 parents (5 dyads) in the formative test, and then 10 adolescents + 10 parents (10 dyads) in the validation test for a total of 15 adolescents and 15 parents. The sample size is based on evidence that testing with 5 users identifies 85% of barriers and facilitators to accessing program materials and putting them to use to inform refinements, and 3 iterations of feedback per user during the testing period identifies 98% [47, 48] Thus, we expect that 15 dyads total with 3 iterations of feedback via semi-structured interviews with the adolescent and also with the parent over the 12-week study period will provide sufficient data to uncover aspects of study processes and the program materials that need refinement prior to efficacy testing. For the formative and evaluative tests, we will use unique sets of dyads to gain a broader perspective than is possible with the same sets. We will also focus on children in the adolescent age group (ages 12-17.9 years) for this more in-depth data collection because they are more likely than younger children to express opinions independent of parental influence.[49]

Equiti Foods will tailor flavorings and deliver selected meals along with condiments to enable individualization by household members. The intervention will be 12-weeks duration, with weekly "doses" (meal deliveries) of up to 10 meals per week, as suggested by MTM studies with adult populations. [32, 44] Twelve weeks duration enables three iterations of feedback about the prior month's experience with MTM-Kids.

Participation will require (a) completing a survey at baseline (T1), receipt of MTM-Kids over 12 weeks, (b) participating in interviews at 4, 8, and 12 weeks (T2, T3, T4) after starting to receive meals to inform refinement, and (c) completing a follow-up survey at 12 weeks (T4). While we will not ask participants to forgo other forms of food-related assistance, we will ask them to tell us about food assistance requested and received. Interested dyads will join the informed consent/assent process, complete baseline surveys, and set up an account on Equiti Food's website where they can select/order the first MTM allotment.

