| - Chemotherapy-induced alterations in taste (13 items)                                                        |                                      |                            |                                       |                 | ×                |
| - Acceptability (2 items) and appropriateness (2 items)                                                       |                                      |                            |                                       |                 |                  |
| Parent Survey                                                                                     |                                      |                            |                                       |                 |                  |
| - Socio-demographics (15 items)                                                                               | ×                                    |                            |                                       |                 | ×                |
| - Food (6 items) and nutrition (6 items) insecurity                                                           | ×                                    |                            |                                       |                 | ×                |
| - Financial coping behaviors (18 items)                                                                       | ×                                    |                            |                                       |                 | ×                |
| - Personal Financial Wellbeing Scale (8 items)                                                                | ×                                    |                            |                                       |                 | ×                |
| - Participation in social roles and activities (12 items)                                                     | ×                                    |                            |                                       |                 | ×                |
| - Acceptable (4 items), appropriate (4 items), feasible (4 items), affordable (4 items), accessible (4 items) | ×                                    |                            |                                       |                 | ×                |

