#### 7.2.1 *Surveys and Interview Questions for Adolescents*

Adolescents will be asked to complete (a) a brief investigator-developed socio-demographic survey at baseline (T1), (b) established measures of alterations in taste and chemotherapy induced alterations in taste at weeks 4, 8, and 12 (T2-4) at the start of their semi-structured interviews, and (c) a person-reported measure of acceptability and appropriateness at week 12 (T4).

Socio-demographic items will ask the adolescent to tell us their current age (in years), sex at birth, race, the language they mainly use at home, and their current grade (year) in school.

---

Chemotherapy-induced alterations in taste will be measured by 13-items from the Chemotherapy-Induced Alterations in Taste Scale (CiTAS) [50]. Adolescents will be asked to use a 5-point scale to indicate how much the taste change bothered them this week. Scores will be calculated by summing item responses and dividing by 13 (lower scores indicate less alteration in taste).

Other chemotherapy-related symptoms will be measured by the 15-item Symptom Screening in Pediatrics (SSPedi) tool. [51] Adolescents will be asked to use a 5-point scale anchored by 0 (not at all) and 4 (worst bother) to indicate how much each symptom bothered them today or yesterday. Scores will be calculated by summing item responses. Scores can range from 0-60; lower scores indicate less symptom severity.

Semi-structured interviews will focus on the adolescent's experience with a study provided meal and their recommendations for improvements.

Adolescent-reported acceptability and appropriateness of the MTM-Kids program will be assessed using items that tap into each of these domain. The original items were developed and validated by Weiner and colleagues for use in studies that examine adopters' perspectives on the acceptability, etc. of implementing entire evidence-based programs in practice.[52] For this feasibility study, the Weiner, et al. items served as the basis for assessing areas that may affect participants' perspectives on specific aspects of the MTM program. Each domain has 4-items. Adolescents will be asked to read each item and indicate their response using 5-point scales anchored by 1=completely disagree and 5=completely agree. Domain scores will be calculated by summing item responses and dividing the sum by 4. Domain score range is 1-4, with higher scores indicating better acceptability or appropriateness.

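### One acceptability item on the adolescent form is worded for a parent, and Table 1 gives the wrong number of adolescent items

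*Protocol*

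**What the plan says.** The form is headed "15.2.1.2 Adolescent Acceptability and Appropriateness" and stands among the adolescent surveys in Appendix II. Its third acceptability item says that "our family felt my child's healthcare team cared about my family". Under the inclusion criteria (5.1) the respondent is a patient aged 12 to 17.

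On the number of items, the adolescent row of Table 1 (Time & Events) reads "Acceptability (2 items) and appropriateness (2 items". Section 7.2.1 says "Each domain has 4-items. Adolescents will be asked to read each item", and the endpoint in 3.2.1 refers to "mean overall scores for the 4 item measures of each domain". The form prints four items under each domain.

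On scoring, 7.2.1 says "Domain scores will be calculated by summing item responses and dividing the sum by 4", with responses anchored at 1 and 5. Endpoint 3.2.1 asks for a domain score of at least 3 in 70% of adolescents at week 12 (T4), for acceptability and for appropriateness.

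**The concern.** An adolescent patient has no child, so the third item does not fit its respondent when read literally. Some adolescents will take it to mean their own team. Others may answer as they think a parent would, choose the middle category, or leave it blank. The answers would then not measure one thing across respondents, in a score that is held to a pass criterion.

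The Table 1 row adds a second difficulty. Staff who build the electronic form or check its completeness from the schedule would expect four adolescent items in total, whereas the endpoint and the scoring rule need eight.

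Both matter more than a slip in background text would. The first sits in the instrument that is handed to participants, and no later analysis plan can change how a question was worded once it has been answered.

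**Working it through.** **Inputs.** The printed items (15.2.1.2), the item counts (Table 1, 3.2.1, 7.2.1), the scoring rule (7.2.1), the criterion (3.2.1), and 15 adolescents (8.2.1).

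**1. Whose voice is the item in?** The interview guides in Appendix III keep the two voices apart. The parent guide (15.3.1) asks about the care of the respondent's child; the adolescent guide (15.3.2) asks about the care that the respondent receives. The form makes no such switch for this item. The natural reading is that a parent item was left unadapted. That is an inference from the wording, since the protocol does not say how the item came to be there. No section says it is reworded, omitted or answered by someone else.

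**2. Item count.**

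| Place | Acceptability | Appropriateness | Total |
|---|---|---|---|
| Table 1, adolescent row | 2 | 2 | 4 |
| Endpoint 3.2.1 | 4 | 4 | 8 |
| Section 7.2.1 | 4 | 4 | 8 |
| Form 15.2.1.2, counted | 4 | 4 | 8 |

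Table 1's figure of 2 + 2 is not reproduced by any other place. The parent row of the same table gives 4 per domain, so the discrepancy is confined to the adolescent row.

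**3. Weight of the item.** Score = (sum of four items)/4. One item carries 1/4 = 25% of it. With responses from 1 to 5, it can move the score by (5 − 1)/4 = 1.0 point.

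**4. When it decides the result.** Let *s* be the sum of the other three items. The criterion is met when *s* + item 3 ≥ 4 × 3 = 12. Item 3 alone decides if *s* + 1 < 12 and *s* + 5 ≥ 12, that is, for *s* from 7 to 10. Of the 5³ = 125 possible patterns for the other three items, 15 + 18 + 19 + 18 = 70 have such a sum (56%, each pattern counted once). The same holds for any item of a four-item scale. The figure shows that an item of this weight matters; it does not estimate how many adolescents would be misclassified.

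**5. What the criterion needs.** 0.70 × 15 = 10.5, so 11 of 15 adolescents must reach the threshold if all 15 answer. Each adolescent is 1/15 = 6.7 percentage points.

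**6. Reach.** Endpoint 3.2.1 covers 2 adolescent and 5 parent domains, 7 in all. The misworded item enters one of them.

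**The case against.** The best case on the other side is that both errors are clerical. A patient can readily guess that the healthcare team meant is their own. The item is one of four in one of seven domains, and the secondary analysis in 8.3.2 is descriptive. No test, sample size or primary benchmark depends on it. All of this is fair and limits the size of the point. It does not make the wording right, and guessing is exactly what produces answers that are not comparable.

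Four stronger readings may tempt a reader, and the documents do not support them.

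- *A skipped item is scored as zero, so three answers of 3 give 9/4 = 2.25.* The protocol states the divisor but no rule for missing items, and 0 is not a value on the scale. That rule is commonly left to a statistical analysis plan, which is not at hand.
- *Under Table 1 no adolescent could pass, because two items give at most 10/4 = 2.5.* This joins the one outlying count to the scoring rule of the four-item form. Nobody has planned that combination.
- *The other acceptability items, phrased for the family, fail to ask the adolescent's own view and so contradict 4.1.* The form asks for the respondent's opinions, the items can be answered, and the intervention is aimed at households. The reason in 4.1, that "they are more likely than younger children to express opinions independent of parental influence", is given for the in-depth data collection, in a paragraph about the interviews, and 15.3.2 asks there for personal views. Recasting these items in the first person would be a preference about the construct.
- *The adolescent endpoint cannot be evaluated.* Three of the four acceptability items and all four appropriateness items are answerable as printed.

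**Conclusion.** The point holds within narrow limits. One item of the adolescent acceptability domain is worded for a parent. It carries a quarter of a score that is judged against a threshold of 3 in 70% of adolescents, and it can move that score by up to 1.0 point. The expected harm is inconsistent or missing answers in that domain. How much cannot be computed, because it depends on how adolescents read the item. Separately, the adolescent row of Table 1 states half the number of items that the endpoint, the measure description and the form use (4 against 8 in total).

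This rests on two assumptions: that the form is given as printed, and that the three places which agree on four items per domain state the intent. The family-phrased items, the handling of missing items and the appropriateness domain are not part of the error. It is a small defect, but worth correcting in time because it cannot be undone after the survey.

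**What to change.** Before the first T4 survey:

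- Reword the third acceptability item in 15.2.1.2 so that it refers to the adolescent's own healthcare team, for example *my healthcare team cared about my family*. Make the same change in the electronic form.
- Correct the adolescent row of Table 1 to 4 acceptability and 4 appropriateness items.

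The scoring rule, threshold and sample size stay as they are. The cost is one form edit, one table edit and a routine notification to the ethics board. If any T4 forms have already been completed on the present wording, report how many, since those answers cannot be corrected.
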